## Abstract

**Background:**

Postoperative adjuvant chemotherapy for patients with stage III Colorectal cancer (CRC) is now internationally accepted as standard care for improving patient outcomes. The Adjuvant Chemotherapy Trial of S-1 for Colorectal Cancer (ACTS-CC) confirmed the non-inferiority of S-1 to tegafur/urcail/leucovorin in terms of overall survival and disease-free survival in patients with stage III CRC after curative surgery. However, the 6-month completion rate of S-1 treatment was 76.5 % in the ACTS-CC. Therefore, treatment completion remains an unresolved problem.

**Methods/Design:**

A randomized phase II trial was designed to evaluate the efficacy and safety of oral daily administration and alternate-day administration of S-1 as adjuvant chemotherapy in curatively resected stage III CRC. Enrolled patients were assigned to either S-1 daily administration (Arm A) or alternate-day S-1 administration (Arm B). Assigned treatment will start within 8 weeks after surgery. In both arms, S-1 dosing (oral) will be based on body surface area (80 mg/day for body surface area < 1.25 m^2^, 100 mg/day for 1.25–1.5 m^2^, or 60 mg/day for > 1.5 m^2^). In Arm A, S-1 will be administered orally for 28 days, followed by a 14-day rest. Administration will be conducted for 24 weeks from the date of therapy start. In Arm B, S-1 will be administered orally on alternate days for 28 weeks from the date of the start of therapy. After treatment, all patients will be observed without additional therapy unless recurrent lesions or other cancer lesions occur. The primary endpoint is treatment completion rate. Secondary endpoints include 3-year disease-free survival, compliance, and adverse events.

**Discussion:**

Previously, S-1 alternate-day intake maintained the efficacy of chemotherapy while reducing adverse effects for patients with R0-resected stage II/III gastric cancer. Improvement of chemotherapy completion rate for patients with colorectal cancer will lead to an improved patient prognosis. Therefore, a randomized phase II trial has been designed to examine the efficacy of alternate-day versus current standard daily S-1 administration as adjuvant chemotherapy for R0-resected stage III colorectal cancer.

**Trial registration:**

This study was registered on 18 February 2014 with University Hospital Medical Information Network Clinical Trials Registry: UMIN000013185

**Electronic supplementary material:**

The online version of this article (doi:10.1186/s12885-015-1476-6) contains supplementary material, which is available to authorized users.

## Background

Colorectal cancer (CRC) is the second most common cancer in Japan, affecting over 100,000 individuals [1]. The Japanese Society for Cancer of the Colon and Rectum (JSCCR) reported recurrence rates of 3.7 % for stage I disease, 13.3 % for stage II disease, and 30.8 % for stage III [2]. Postoperative adjuvant chemotherapy for patients with stage III CRC is now internationally accepted as standard care for improving patient outcomes. The 2010 JSCCR guidelines recommend four regimens as adjuvant therapy for stage III CRC: i.v. 5-fluorouracil/leucovorin, oral tegafur-uracil/leucovorin, capecitabine, and FOLFOX (5-fluorouracil/leucovorin plus oxaliplatin) [2].

S-1 is an oral anticancer agent containing tegafur, gimeracil, and oteracil potassium in a molar ratio of 1:0.4:1 [3]. The Adjuvant Chemotherapy Trial of S-1 for Colorectal Cancer (ACTS-CC) confirmed the non-inferiority of S-1 to tegafur/urcail/leucovorin in terms of overall survival and disease-free survival in patients with stage III CRC after curative surgery [4]. However, the 6-month completion rate of S-1 treatment was 76.5 % in the ACTS-CC [4]. Therefore, treatment completion remains an unresolved problem.

Previously, S-1 alternate-day intake maintained the efficacy of chemotherapy while reducing adverse effects, and was tolerable for patients with R0-resected stage II/III gastric cancer [5]. Therefore, we planned a multicenter, cooperative, prospective, randomized phase II study to compare daily and alternate-day S-1 administration as postoperative adjuvant therapy for CRC.

## Methods/Design

### Registration of the protocol

This study protocol was registered on the website of the University Hospital Medical Information Network, Japan (protocol ID: UMIN000013185) on 18 February 2014. Details are available at: https://upload.umin.ac.jp/cgi-open-bin/ctr/ctr.cgi?function=brows&action=brows&type=summary&recptno=R000015242&language=J

### Digest of the study protocol

#### Objective

A randomized phase II trial was designed to evaluate the efficacy and safety of oral daily administration and alternate-day administration of S-1 as adjuvant chemotherapy in curatively resected stage III CRC. This study protocol was approved by the Institutional Protocol Review Board of Osaka General Medical Center (the affiliation of the Principal Investigator) and other participating institutions (Additional file 1).

#### Study setting

This study is a multi-institutional, prospective, randomized controlled trial that will begin on 1 April, 2014.

#### Endpoints

The primary study endpoint is treatment completion rate. Secondary endpoints include 3-year disease-free survival, overall survival, compliance, and adverse events defined by the Common Terminology Criteria for Adverse Events v.4.0 [6].

### Eligibility criteria

Patients who received curative resection for histopathologically demonstrated stage III (Japanese Classification of Colorectal Cancer 8^th^ edition [7]) colon or rectosigmoid adenocarcinoma were eligible to participate in this study. The main eligibility criteria were: age 20–80 years, starting chemotherapy within 8 weeks after surgery, having an Eastern Cooperative Oncology Group performance status of 0–1, adequate oral intake, preserved major organ functions, and the ability to provide informed consent.

Patients were excluded if they had a previous history of therapy for stage III CRC (except surgery), previous or concomitant CRC (except carcinoma *in situ*), an active malignancy within 5 years, a history of severe anaphylaxis or allergies to any drug, significant active illness that would preclude protocol treatment, undergoing treatment with fluorocytosine, hepatitis B or C virus infection, or severe mental disease. Pregnant or lactating females were also excluded.

Protocol treatment will begin when the patient fulfills the following criteria: total leukocytes <12,000/mm^3^, neutrophils ≥ 1500/mm^3^, platelets ≥100,000/mm^3^, hemoglobin ≥ 9.0 g/dL, aspartate aminotransferase and alanine aminotransferase < 100 IU/L, total bilirubin < 2.0 mg/dL, and creatinine clearance ≥ 60 mL/min.

### Registration

After confirming eligibility, enrolled patients were randomly assigned to receive either standard daily S-1 therapy (Arm A) or alternate-day S-1 therapy (Arm B) at the MCSGO Data Center. Randomization was performed via a minimization method with stratification by lymph node status (N1 vs. N2 and N3), age (< 70 years vs. ≥ 70 years), and institution (Fig. 1).

**Fig. 1 Fig1:**
[figure not shown]
Study design

### Treatment methods

Enrolled patients were assigned to either S-1 daily administration (Arm A) or alternate-day S-1 administration (Arm B). Assigned treatment will start within 8 weeks after surgery. In both arms, S-1 dosing (oral) will be based on body surface area (80 mg/day for body surface area < 1.25 m^2^, 100 mg/day for 1.25–1.5 m^2^, or 60 mg/day for > 1.5 m^2^).

In Arm A, S-1 will be administered orally for 28 days, followed by a 14-day rest. Administration will be conducted for 24 weeks from the date of therapy start. In Arm B, S-1 will be administered orally on alternate days for 28 weeks from the date of the start of therapy (Fig. 1). After treatment, all patients will be observed without additional therapy unless recurrent lesions or other cancer lesions occur.

In each course, treatment will continue when the patients fulfill the following criteria: total leukocytes ≥ 3000/mm^3^, platelets ≥ 100,000/mm^3^, aspartate aminotransferase and alanine aminotransferase < 100 IU/L, total bilirubin < 2.0 mg/dL, creatinine ≤ 1.5 mg/dL, and diarrhea and stomatitis no greater than grade 1. If the criteria for continuing treatment are not met, then treatment will be postponed or temporarily suspended until the criteria are satisfied.

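### The S-1 dose bands run 80, 100, 60 mg/day as body surface area rises, so the largest patients get the least drug

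*Protocol article*

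**What the plan says.** The Treatment methods section of the protocol article states the principle first: "In both arms, S-1 dosing (oral) will be based on body surface area". It then assigns three daily doses to three bands, from lowest to highest: "80 mg/day for body surface area < 1.25 m^2^, 100 mg/day for 1.25–1.5 m^2^, or 60 mg/day for > 1.5 m^2".

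The Methods/Design part of the abstract gives the same three doses for the same bands in the same order. No other visible text gives a dose rule, and none gives a reason for a lower dose in larger patients.

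**The concern.** A dose based on BSA should rise, or at least not fall, as BSA rises. Here the highest band has the lowest dose of the three, below even that for the smallest patients. The doses therefore fit neither the order of the bands nor the stated principle.

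Dose drives toxicity. The same section makes each further course conditional on blood counts, liver tests, creatinine, diarrhea and stomatitis, with delay or suspension when the limits are not met. Dose therefore bears on treatment completion, the primary endpoint. It also bears on adverse events and disease-free survival, which both enter the Decision principle. If patients were dosed as printed, all three outcomes would depend on body size in a way nobody intended, and individual patients would be over- or underdosed. A reader who later adopts the regimen from this article would take over the same error.

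**Working it through.** **Inputs.** All come from Treatment methods and are repeated in the abstract: 80 mg/day below 1.25 m², 100 mg/day from 1.25 to 1.5 m², 60 mg/day above 1.5 m².

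**Step 1: order of the doses.** As BSA rises, the dose goes 80 → 100 → 60 mg/day. The change is +20 mg at 1.25 m² and −40 mg at 1.5 m². A patient above 1.5 m² gets 80 − 60 = 20 mg/day less than one below 1.25 m².

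**Step 2: dose per m² as written.** Dose intensity = daily dose / BSA, taken at the printed band limits.

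| BSA band | Daily dose | Calculation | mg/m²/day |
|---|---|---|---|
| < 1.25 m² | 80 mg | 80/1.25 = 64 | more than 64 |
| 1.25–1.5 m² | 100 mg | 100/1.5 = 66.7; 100/1.25 = 80 | 66.7 to 80 |
| > 1.5 m² | 60 mg | 60/1.5 = 40 | less than 40 |

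The top band does not overlap the other two. At 1.5 m² the daily dose falls by (100 − 60)/100 = 40%.

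**Step 3: would an ascending order fit the principle better?** This step is an illustration only. It assumes outer limits of 1.0 and 2.0 m², which the article does not give.

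| Assignment, low to high band | < 1.25 m² | 1.25–1.5 m² | > 1.5 m² |
|---|---|---|---|
| As printed: 80/100/60 | 64–80 | 66.7–80 | 30–40 |
| Same doses ascending: 60/80/100 | 48–60 | 53.3–64 | 50–66.7 |
| Hypothetical: 80/100/120 | 64–80 | 66.7–80 | 60–80 |

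Either ascending set gives a roughly even dose per m² across bands; the printed set does not. That points to misassigned doses. Because more than one set restores the pattern, the article alone cannot show which was intended.

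**Step 4: size of the misdosing if 60/80/100 was meant.** On that assumption every band is wrong as printed:

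- smallest patients: 80/60 = 1.33, or 33% too much
- middle band: 100/80 = 1.25, or 25% too much
- largest patients: 60/100 = 0.60, or 40% too little

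**The case against.** The best reply is that this is a slip in a condensed article and not a design decision. Nothing shows that sites dosed from this sentence, and the approved full protocol may carry the right bands. Treatment methods also points to Fig. 1 for the regimen, and that figure is not available here, so one can say only that no visible text corrects the bands. All of this stands, and it makes every clinical consequence conditional on the text being followed. It does not remove the error: the article states a dose rule wrongly in two places, both in running prose, so a broken table does not explain it. If the figure shows other doses, it contradicts the text and the two still need reconciling.

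A second reply is that the rule is the same in both arms of a randomized trial, and the Decision principle compares Arm B with Arm A. That also stands: a shared dosing error does not by itself bias the comparison. What it would affect is patient safety, the absolute completion and toxicity rates in each arm, and the reproducibility of the regimen.

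Third, the article gives the 76.5% completion rate of the earlier adjuvant S-1 trial (ACTS-CC) but not that trial's dose bands. Whether dosing as printed would make the two trials incomparable cannot be judged from this document, and the conclusion here does not rely on it.

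**Conclusion.** The point holds. The printed bands contradict the stated basis for dosing in both places where they appear. The largest patients would receive less than 40 mg/m²/day, against more than 64 in the two smaller bands, with a 40% drop in daily dose at 1.5 m². These figures need only the printed values. The likely explanation is that the doses were transposed in drafting, but that is an inference, and the intended values remain open. The correction is essential because this is the dosing instruction for a cytotoxic drug, on grounds of patient safety and reproducibility. It is not evidence that the randomized comparison is biased, or that patients were in fact misdosed.

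**What to change.** Check the three band-to-dose assignments against the dosing rule in the approved full protocol, and correct both Treatment methods and the Methods/Design part of the abstract. Check that Fig. 1 agrees if it shows doses. Confirm that the documents used at the sites and at the MCSGO Data Center carry the reconciled bands. If any site followed the printed version, identify the patients concerned and review their dosing and safety records.

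The cost is an erratum and a check of site documents. Sample size, endpoints and analysis need no change for this correction.

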### Study design and statistical methods

The primary endpoint of this study is treatment completion rate, which is expected to be higher than the treatment completion rate in the ACTS-CC [4] due to alternate-day S-1 administration. Assuming a null hypothesis of 73 % treatment completion and an alternative hypothesis of 83 % treatment completion with one-sided type I error = 0.1 and type II error = 0.2, it was necessary to enroll at least 77 patients in each arm. Assuming 10 % loss to follow-up, we calculated that a total of 170 patients were needed in both treatment arms.

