### Decision principle

At the beginning of the study, we established the decision principle to be used after trial results are obtained. If the treatment completion rate for alternate-day S-1 administration (Arm B) is better than that for daily S-1 administration (Arm A), and if the 3-year disease-free survival and adverse-events rates of Arm B is improved or approximately the same as those of Arm A, then alternate-day S-1 administration will be recommended as adjuvant chemotherapy for stage III R0-resected CRC patients.

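### The 77 patients per arm fit a test against a fixed 73%, but the decision rule compares Arm B with Arm A, and the stated error rates do not hold for that comparison

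*Protocol article*

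**What the plan says.** Study design and statistical methods (protocol article) gives every planning input for the primary endpoint, treatment completion rate: "Assuming a null hypothesis of 73 % treatment completion", "an alternative hypothesis of 83 % treatment completion" and "one-sided type I error = 0.1". The sentence then gives the second error rate and the conclusion together: "type II error = 0.2, it was necessary to enroll at least 77 patients in each arm". With "Assuming 10 % loss to follow-up" the total becomes 170, or 85 per arm. The same paragraph expresses the hoped-for gain relative to the completion rate in ACTS-CC, an external trial. It does not say that 73% is the assumed rate in Arm A, that the calculation is one-sample, or which arm is to be tested.

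The Decision principle section sets out how the result will be used. Its first condition reads: "If the treatment completion rate for alternate-day S-1 administration (Arm B) is better than that for daily S-1 administration (Arm A". If that holds, and disease-free survival and adverse events in Arm B are improved or about the same, the alternate-day schedule will be recommended. Background and Discussion likewise describe a randomised trial whose purpose is to compare the two schedules.

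**The concern.** The paragraph that fixes the sample size and the section that fixes the decision do not describe the same comparison. A test of one arm against a fixed rate carries the sampling error of one arm. A comparison of two randomised arms carries the error of both, so it needs about twice as many patients per arm for the same difference and error rates.

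Anyone reading the two sections together will take the type I error of 0.1 and the type II error of 0.2 as properties of the B-versus-A decision. At stake is how the result is interpreted. If a formal two-sample test is used, a non-significant result would be read as coming from a trial with 80% power when the power is nearer 60%. If a numerically higher rate is enough, a favourable result would be read as controlled at 0.1 when it is not controlled at that level. The rule leads to a treatment recommendation, so either misreading matters.

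**Working it through.** **Inputs**, all from Study design and statistical methods: p0 = 0.73, p1 = 0.83, one-sided alpha 0.10 (z = 1.2816), type II error 0.20 (z = 0.8416), 77 per arm, 10% loss, 170 in total.

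**1. Reproducing 77 as a one-sample size**

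- Arcsine formula: n = [(1.2816 + 0.8416) / (2(asin√0.83 − asin√0.73))]² = [2.1232 / (2(1.1458 − 1.0244))]² = 76.45, so **77**.
- Normal approximation: n = [1.2816√(0.73×0.27) + 0.8416√(0.83×0.17)]² / 0.10² = 78.3, so 79.
- Exact binomial with n = 77 (success at 62 or more completers): alpha 0.084, power 77.2%. The smallest n with exact power of at least 80% is 80.

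The stated number is therefore a one-sample size to within rounding and choice of formula.

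**2. The two-arm requirement for the same inputs**

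- Pooled: n per arm = [1.2816√(2×0.78×0.22) + 0.8416√(0.73×0.27 + 0.83×0.17)]² / 0.10² = (0.7508 + 0.4894)² / 0.01 = 153.8, so **154 per arm**.
- Unpooled: 152.5, so 153. With continuity correction: 174.

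None of these two-sample formulas gives 77 per arm. But 154 = 2 × 77, so a per-arm number read as a total would also yield 77.

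**3. Loss to follow-up**

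77 × 1.10 = 84.7, so 85 per arm and 170 in total. Division by 0.90 gives 86 per arm and 172. The difference is trivial.

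**4. What the planned size gives for B versus A** (73% v 83%)

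| Rule for B versus A | 77 per arm | 85 per arm |
|---|---|---|
| Two-sample z-test, one-sided 0.10, normal approximation: power | 58.6% | 61.6% |
| Same test, pooled z, exact enumeration: power | 59.3% | 61.7% |
| Fisher's exact test, one-sided 0.10: power | 51.5% | 54.9% |
| Difference from 73% detectable with 80% power (z-test) | 13.7 points | 13.1 points |
| B numerically higher: probability at 73% v 83% | 92.1% | 93.2% |
| B numerically higher: probability when both are 73% | 46.4% | 46.6% |

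The enumerated z-test has actual size 0.099 at 77 per arm, so its power figure is not depressed by a conservative test.

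**5. Side by side**

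- B against a fixed 73%: the stated error rates hold approximately, but this is not the comparison in the Decision principle.
- B against A by a formal test at 0.10: alpha holds, but the type II error is about 0.41 at 77 per arm (1 − 0.593), not 0.2.
- B against A by numerical order: the miss rate is about 8% (1 − 0.921), but the false-positive rate is about 46%, not 0.1.

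**The case against.** The strongest reply is that the plan never claims 80% power for B versus A. The sample-size paragraph refers to ACTS-CC and gives a single fixed null value, which is how one sizes an arm against a benchmark. Sizing each arm of a randomised phase II trial in this way, with a concurrent reference arm, is a recognised design. On that reading 77 is correct to rounding. This stands as far as it goes: a reader might infer that the plan expressly promises 80% power for the randomised comparison, and it does not. But the article nowhere says the test is one-sample, and its decision rule does not refer to 73% at all. If the benchmark design was meant, the two sections still disagree.

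A second reply is that the decision rule names no test, so it is not established that a true 10-point gain would be missed about four times in ten. That is also right. The figure belongs to a formal two-sample test at 0.10, which the rule does not state. Under a numerical rule the miss rate is about 8%. But a stated null hypothesis and type I error do not fit a rule that favours Arm B in nearly half of trials with no true difference. The mismatch then moves from power to alpha.

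Third, a reader might infer from 154 = 2 × 77 that a per-arm requirement was mistakenly halved. The article cannot separate that from a deliberate one-sample calculation, and the B-versus-A figures are the same either way.

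Finally, the full protocol or analysis plan may define the test. The point does not rest on that omission; it rests on two statements in the article that do not fit each other. Nor does completion alone drive the recommendation, since disease-free survival and adverse events must also be acceptable. But completion is the primary endpoint and the only one with stated error rates.

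**Conclusion.** The point holds as an inconsistency between the sample-size paragraph and the decision rule. The stated error rates fit Arm B against a fixed 73%; they do not fit Arm B against Arm A under either reading of better. For a formal two-sample z-test at one-sided 0.10, power is about 59% at 77 per arm and about 62% if all 85 are evaluable, and 80% power is reached only for a difference of about 13 to 14 points. For a numerically-higher rule, the chance of favouring B is about 92% under the planned rates and about 46% under equality at 73%.

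These figures assume true rates of 73% and 83% (73% in both arms for the equality case), equal arms and independent binomial outcomes. The article does not support going further: it does not show that a halving error occurred, and it does not fix the miss rate at four in ten.

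**What to change.** Reconcile Study design and statistical methods with Decision principle in one of two ways.

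- **(a) If the formal test is B versus A at one-sided 0.10:** replace the type II error of 0.2 with power of about 59% at 77 evaluable per arm (62% at 85) for 73% v 83%, and give the difference detectable with 80% power as about 13 to 14 points. In Decision principle, say that better refers to this test.
- **(b) If the powered test is Arm B alone against the fixed 73%:** say so in the sample-size paragraph. Make that test the formal completion-rate criterion in Decision principle, and report the B minus A difference with its confidence interval as the concurrent reference.

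Both are changes of wording and add no patients. The cost is a less favourable statement: lower declared power under (a), or under (b) a primary conclusion that no longer rests on the randomised comparison.

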### Decision principle

At the beginning of the study, we established the decision principle to be used after trial results are obtained. If the treatment completion rate for alternate-day S-1 administration (Arm B) is better than that for daily S-1 administration (Arm A), and if the 3-year disease-free survival and adverse-events rates of Arm B is improved or approximately the same as those of Arm A, then alternate-day S-1 administration will be recommended as adjuvant chemotherapy for stage III R0-resected CRC patients.

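### The completion condition in the decision principle is not tied to the test the trial was sized for; read numerically, that condition alone is met about 46% of the time when the arms do not differ

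*Protocol article*

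**What the plan says.** Two sections of the protocol article bear on how the primary endpoint, treatment completion, is judged.

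*Study design and statistical methods* gives the hypothesis and the size. Completion is the endpoint "which is expected to be higher than the treatment completion rate in the ACTS-CC", an external trial. The design values are "Assuming a null hypothesis of 73 % treatment completion and an alternative hypothesis of 83 % treatment completion with one-sided type I error" of 0.1 and type II error 0.2, from which "it was necessary to enroll at least 77 patients in each arm". The total follows: "Assuming 10 % loss to follow-up, we calculated that a total of 170 patients were needed in both treatment arms".

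*Decision principle* gives the rule that was set at the start for use once results are known. Its completion condition begins "If the treatment completion rate for alternate-day S-1 administration (Arm B) is better than that for daily S-1 administration (Arm A"). The same sentence adds, joined by *and*, that 3-year disease-free survival and adverse-event rates in Arm B be improved or about the same. If all of this holds, alternate-day S-1 will be recommended. The section does not mention the 73% null, the error rate of 0.1, or any test or margin for any of the conditions.

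**The concern.** The error rate is attached to one question (is completion above 73%?) and the recommendation to another (is Arm B better than Arm A?). Nothing connects them. Followed as written, the rule can be satisfied when the sized test is not met.

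This matters because the output is a treatment recommendation and completion is the primary endpoint. If a one-patient lead for Arm B is enough, chance alone satisfies the primary condition nearly half the time when the schedules do not differ. A reader who sees the stated 0.1 may take it to protect the recommendation, and the text gives no ground for that.

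**Working it through.** **Inputs** (all from the protocol article): null 73%, alternative 83%, one-sided type I error 0.1, type II error 0.2, 77 per arm, 170 in total, so 85 per arm if split equally. The external trial's S-1 completion rate is given as 76.5% in the Background.

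**1. Reproducing the 77.** With z(0.90) = 1.2816 and z(0.80) = 0.8416, (1.2816 + 0.8416)² = 4.508.

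- One sample against a fixed 73%, arcsine formula: n = 4.508 / [4 (arcsin√0.83 − arcsin√0.73)²] = 4.508 / [4 × (1.1458 − 1.0244)²] = 76.5, so 77. This matches.
- One sample, normal approximation: [(1.2816√(0.73×0.27) + 0.8416√(0.83×0.17)) / 0.10]² = 78.3, so 79. This is close.
- Two arms, one-sided: [(1.2816√(2×0.78×0.22) + 0.8416√(0.73×0.27 + 0.83×0.17)) / 0.10]² = 153.8, so 154 **per arm**. This does not match, although 154 equals the plan's two-arm total before loss (2 × 77).
- Total: 154 × 1.1 = 169.4, so 170, as stated.

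The sized test is therefore, on the numbers, a one-sample test against 73%.

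**2. The decision rule read as a numerical comparison.** Let X_A and X_B be independent binomial counts of completers. P(X_B > X_A) was obtained by exact enumeration.

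| True A / true B | 77 per arm | 85 per arm |
|---|---|---|
| 73% / 73% | 0.464 | 0.466 |
| 76.5% / 76.5% | 0.462 | 0.464 |
| 76.5% / 71.5% | 0.212 | 0.203 |
| 73% / 83% | 0.921 | 0.932 |

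For common true rates from 70% to 83% the equal-rate figure stays between 0.457 and 0.467.

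**3. From the condition to the whole rule.** The probability of a recommendation under equal completion is about 0.46 × q, where q is the chance that the disease-free survival and adverse-event conditions are also met, given that B exceeds A. The article does not fix q. As assumptions, q = 0.25, 0.5 and 0.9 give 0.12, 0.23 and 0.42. The product falls to 0.10 only when q is about 0.10 / 0.46 = 0.22.

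**4. The decision rule read as a one-sided 0.10 test of B versus A.** For a pooled z-test, exact size at 73%/73% is 0.099 (77 per arm) and 0.100 (85). Power for 73% v 83% is 0.59 and 0.62, against the stated 0.80.

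**5. The rule tied to the sized test.** The smallest r with P(X_B ≥ r | 73%) ≤ 0.10 is 62 of 77 (size 0.084, power at 83% 0.77) or 68 of 85 (size 0.089, power 0.81). Requiring also that Arm B not be below Arm A, with Arm A truly at 73%, gives power 0.76 and 0.80. If both arms truly complete at 76.5%, the combined condition is met with probability 0.22 (77) or 0.24 (85).

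**The case against.** The strongest reply is that the article nowhere says numerically better. The section just before it sets a one-sided error of 0.1 for the same endpoint, so *better* could mean shown better by that test, and a condensed article may leave the mechanics to the full protocol or analysis plan. This stands to the extent that 46% follows from one reading of an undefined word. It does not remove the point. The article itself fixes the rule and its consequence, and the two sections use different comparators. If *better* means a one-sided 0.10 test between arms, the size is about right but the power is 59% to 62%, not the 80% the sample size claims.

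A second reply is that completion is only one of the conditions. That is correct, and it makes 46% a ceiling for the recommendation. The other conditions offer no protection that can be calculated, because *approximately the same* has no margin.

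A reader might infer that the trial's false-positive rate is 46% instead of the stated 10%. The documents do not support that. The 46% concerns one condition on one reading, and the 10% belongs to a test against 73%, not to a comparison of B with A. The two figures describe different hypotheses.

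**Conclusion.** The point holds in this form: the completion condition of the recommendation is not linked to the test that the trial was sized for. The size depends on the reading.

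- Read numerically, the condition is met 46% to 47% of the time under equal true rates of 73% to 76.5%, and 20% to 21% of the time when Arm B is truly 5 points worse (71.5% v 76.5%). These are upper bounds for the full rule.
- Read as a one-sided 0.10 between-arm test, error is about 10% but power is about 59% to 62%.

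On neither reading do the two sections together give a between-arm decision with 10% error and 80% power. The figures assume independent binomial outcomes, equal allocation, and 77 to 85 patients per arm in the analysis. The reading of the 77 as a one-sample size rests on reproducing the figure, since the article does not name its formula.

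**What to change.** **If the sample size is kept.** In the Decision principle, replace the completion condition with: Arm B rejects the 73% null by the exact one-sided 0.10 binomial test, and its observed completion rate is not below that of Arm A. Give the critical numbers (at least 62 of 77, or 68 of 85) and say that they are recalculated for the number actually analysed. Add a sentence that this controls error against 73% only and not against Arm A, and disclose that the condition is met with probability about 0.22 to 0.24 if both arms truly complete at 76.5%, the rate the article cites for the external trial.

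The cost is two or three sentences. Under 73% v 83% the chance of meeting the completion condition falls from 92% to 93% (numerical reading) to 76% to 80%. A pass cannot be reported as superiority over daily S-1.

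**If a between-arm claim is wanted.** Define *better* as a one-sided 0.10 test of Arm B versus Arm A, which needs an observed difference of about 1.2816√(2×0.78×0.22/n) = 8.6 points at 77 per arm or 8.1 at 85. Restate power in the sample-size section as about 59% to 62% for 73% v 83%. Keeping 80% would take about 154 per arm (308 in total) before allowance for loss, twice the present size.

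Either way, the two sections should name the same comparator and the same test.
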